## Abstract

**Background:**

The capacity for invasive tissue biopsies followed by histopathology diagnosis in sub-Saharan Africa is severely limited. Consequently, many cancer patients are diagnosed late and outcomes are poor. Here, we propose to evaluate circulating tumour (ct) DNA analysis (“liquid biopsy”), a less invasive and faster approach to diagnose endemic EBV-driven lymphomas (EBVL) in East Africa.

**Methods:**

We will evaluate the clinical utility of an already validated ctDNA test prospectively in a head-to-head comparison against histopathology. The primary endpoint is the time from presentation to the specialist centre to a final diagnosis of EBV- Lymphoma. Secondary endpoints include the sensitivity and specificity of liquid biopsy and health economic benefits over histopathology. One hundred forty-six patients will be recruited over 18 months. Patients will be eligible if they are 3–30 years of age and have provided written consent or assent as per IRB guidelines. Tissue and venous blood samples will be processed as per established protocols. Clinical data will be captured securely and in real-time into a REDCap database. The time from presentation to diagnosis will be documented. The sensitivity and specificity of the methods can be estimated within 5% error margin with 95% confidence level using 73 cases and 73 controls. Health-economic assessment will include micro-costing of ctDNA test and histopathology. All results will be reviewed in a multidisciplinary tumour board.

**Discussion:**

The study evaluates the clinical utility of ctDNA in improving the speed of diagnostic pathways for EBVL in sub-Saharan Africa. Our results would provide proof-of-principle that ctDNA can be used as a diagnostic tool in areas without access to regular pathology, that transfer of the tool is feasible, and that it leads to an earlier and faster diagnosis. The potential clinical and economic impact of this proposal is thus significant. If successful, this study will provide appropriate, and cost-effective diagnostic tools that will promote earlier diagnosis of EBVL and potentially other cancers in countries with restricted healthcare resources.

**Trial registration:**

Pan African Clinical Trials Registry: PACTR202204822312651, registered on 14th-April-2022.

## Background

Epstein Barr virus-driven lymphomas (EBVL) account for nearly 10% of cancer diagnoses in sub-Saharan Africa [1–3]. They disproportionally affect children and young adults and are invariably fatal without treatment [4, 5]. Importantly, 90% of patients with infection-related lymphomas can be cured provided they are diagnosed early and that the precise lymphoma subtype is identified [6, 7]. However, mortality in the region is very high, with an average 4-year survival rate estimated at 44% for endemic Burkitt Lymphoma in Uganda [8].

Despite established diagnostic pathways, treatments, and improved outcomes in high-income countries, diagnostics, treatment, and supportive care are severely limited in SSA, and outcomes are poor [9–11]. Tissue diagnosis in particular poses a significant challenge with a single pathologist being responsible for millions of patients within a region [12, 13]. Even though tissue biopsy is the gold standard for diagnosis, obtaining prompt results is a major hurdle [14]. Samples are often transported to a tertiary facility within the country or even overseas for reporting.

Research studies mostly using international haematopathology review have demonstrated that the most common aggressive childhood lymphomas are infection-related: endemic Burkitt lymphoma (BL, EBV), Hodgkin’s lymphoma (HL; EBV, HIV), acute lymphoblastic lymphoma (LBL), and diffuse large B-cell lymphoma (DLBCL; HIV, EBV ) [4, 10, 15]. Lymphomas can mimic other conditions (tuberculosis, leishmaniasis) or be associated with infections (EBV, malaria) that are common in sub-Saharan Africa [16]. This further contributes to the challenge of making a diagnosis of lymphoma correctly without histopathology.

To tackle some of the aforementioned challenges, we established a partnership with Muhimbili National Hospital (MNH), Muhimbili University of Health and Allied Sciences (MUHAS), Kilimanjaro Christian Medical Centre (KCMC), the Tanzanian Paediatric Oncology Network, African Field Epidemiology Network (AFENET), and the Epidemiology of Burkitt Lymphoma in East-African Children and Minors (EMBLEM) site at St Mary’s Hospital Lacor in Uganda and the Oxford Molecular Diagnostics Centre in the UK. The objective of this partnership is to evaluate a novel diagnostic test using cell-free circulating tumour DNA (ctDNA) that has the potential to allow early and precise diagnosis of lymphomas in resource-limited settings. This tool promises to allow the diagnosis of lymphoma from blood and to provide genetic information to aid with the accurate identification of lymphoma subtypes. We, therefore, hypothesize that our approach to the analysis of ctDNA will speed up the diagnosis of children and young adults with EBVL and that this would increase the number of children treated early ultimately leading to increased overall survival.

Unlike standard invasive biopsies, ctDNA sequencing uses a small sample of the patient’s blood. As such it offers a promising non-invasive tool to evaluate tumour heterogeneity permitting multiple sampling and monitoring of treatment response [17]. Processes such as apoptosis, tissue necrosis, and possibly active secretion by cancerous and normal cells are thought to release nucleic acids (short-double stranded DNA fragments) into circulation [18]. These fragments usually have a short half-life in circulation, in part because of rapid hepatic and renal clearance [19]. Therefore, ctDNA reflects a real-time genetic signature of the tumour.

## Methods

### Aim of the study

To improve diagnosis of childhood and young adult lymphomas in sub-Saharan Africa by making it faster using liquid biopsy.

### Specific objectives

#### Primary objective

To evaluate non-invasive cell-free circulating tumor DNA (ctDNA) detection as a diagnostic screening tool for suspected lymphoma by comparing it to gold standard invasive biopsy followed by best available local pathology. The primary endpoint is the time from presentation to the specialist centre to a final diagnosis of EBVL.

#### Secondary objectives

To assess the sensitivity and specificity of the liquid biopsy approach for the diagnosis of other lymphomas.To evaluate the health-economic benefits of the novel liquid biopsy technology in an LMIC setting.

#### Exploratory objectives

Describe the mutational landscape of paediatric and young adult EBVL in East Africa. We will document the most commonly observed genetic aberrations based on ctDNA sequencing results.Transfer of novel diagnostic techniques to local laboratories. We hope to develop a novel diagnostic teaching and training program for local scientists including a published curriculum, timetable, and assessments.

### Research design

This is a multicenter prospective case-control head-to-head comparison study. The clinical utility of ctDNA will be evaluated prospectively against the best local pathology with the time from the first presentation to the specialist center to the final diagnosis as the primary study endpoint.

### Study duration

We anticipate that recruitment will take 18 months and each patient will be followed up for 6 months after completion of treatment.

### Study sites

#### Muhimbili National Hospital (MNH) in Dar Es Salaam, Tanzania

Muhimbili National Hospital (MNH) is a National Referral Hospital, Research Centre, and University Teaching Hospital with a 1500 bed facility. In 2017, a total of 497 children were referred from various parts of the country to MNH and treated for different types of cancers. Of these, 90 had lymphoma (~ 20%), with 81 (~ 80%) of these confirmed BL. The Tanzanian Paediatric Oncology Network is a fully operating referral network with MNH at its centre that currently covers 40% of the country including sites where EBVL is endemic e.g., Bugando Medical Centre, Mwanza, and Sengerema in Western Tanzania.

#### Kilimanjaro Christian medical center (KCMC) in Moshi, Tanzania

KCMC is nested on the slopes of Mount Kilimanjaro in the North-Eastern part of Tanzania. It is owned by the Good Samaritan Foundation, a nonprofit organization of the Evangelical Lutheran Church. KCMC serves as a zonal referral consultant and teaching hospital for a population of 15 million people in five neighboring regions. KCMC has a 700-bed capacity offering a range of clinical sub-specialties. Cancer Care Centre (CCC) was established in December 2016 initially offering outpatient services. In January 2021 a 45-bed capacity inpatient wing with four HEPA filtered isolation rooms was commissioned. Between 2018 and 2020, a total of 108 children and young adults aged 3 to 30 received treatment at CCC. Out of these, 30(27.8%) were diagnosed and treated as cases of lymphoma.

#### St Mary’s hospital Lacor in Gulu, Uganda

Lacor hospital located in the Northern city of Gulu is a catholic founded, private not-for-profit, regional referral, and university teaching hospital. It is a 482- bed capacity with ten departments and specialised care units including paediatric oncology. Annually, the hospital treats between 100 and 150 children diagnosed with lymphomas. Burkitt lymphoma is the most common lymphoma diagnosed in the region, accounting for over half of the cases diagnosed in the year 2018. Partnering with two charity foundations; Oncology for Africa (AFRON) and Soleterre, the hospital extends psychosocial support to cancer children including accommodation and feeding during hospitalization.

### Patient eligibility

**Inclusion criteria:** Children and young adults aged 3–30 years (up to the day before their 31st birthday) suspected of having EBVL based on clinical presentation. Although a maximum duration between screening and recruitment has not been specified, given the natural history of EBVL we would anticipate that the majority of patients are recruited within 7–14 days of initial presentation. This takes into account local timelines for obtaining and reporting tissue biopsy results. All screening and eligibility assessments must be completed before the patient receives any treatment for lymphoma.

**Exclusion criteria:** Patients started on chemotherapy, and those unable, or unwilling, to provide written informed consent (and/or assent) will be excluded from the proposed study.

### Procedure for patient identification and obtaining consent

Children and young adults presenting with signs and symptoms suggestive of lymphoma (mostly commonly facial or abdominal swellings) will be identified through Outpatient Departments, Medicine, and Paediatric Oncology services. A study medical doctor will review the patient’s records to determine eligibility for the proposed study. Eligible patients will be approached before starting EBVL chemotherapy, for informed consent. Reasons for non-participation will be recorded for all screened patients (Fig. 1).

**Fig. 1 Fig1:**
[figure not shown]
Schema for cohort observation and evaluation in the study

### Baseline data collection

#### Clinical data

An electronic database was created on Redcap Version 11.2.2 and used to collect real-time clinical data by the study staff. In summary, data collected include baseline patient demographics, general medical history, social and family history, early childhood history, and history of presenting illness. We also collect various time points from first symptoms and presentation to diagnosis and start of treatment. Specifically, we will measure the time from presentation to a treatment center to final diagnosis by either best local pathology or liquid biopsy and processing times for tissue and liquid biopsies in the laboratory.

#### Standard of care (SOC) imaging studies

SOC includes chest x-ray plus abdominal ultrasound (Lacor) or computed tomography (CT) scan (MNH, KCMC). This will depend on the site to which the patient initially presents.

#### Best local gold standard diagnosis

Open or trucut biopsy histopathological assessment that includes a limited panel of immunohistochemistry (IHC) stains and genetic analyses on the tissue as may be required. For BL, the diagnostic algorithm developed by Naresh et al. [20] is followed. For Classical Hodgkin Lymphoma (CHL), diagnosis relies on the presence of characteristic morphological features including the presence of Reed-Sternberg cells that express CD30 and often CD15. For the Nodular Lymphocyte predominant HL sub-type (NLPHL), the presence of ‘popcorn cells’ that consistently express CD20 and CD45 by IHC but are negative for CD30 and CD15 is diagnostic. For Diffuse large-B cell lymphoma (DLBCL), tumour morphology and expression of associated markers including CD10 and Bcl6 are used to classify DLBCL into germinal center B cell (GC-DLBCL) and Non-GC- DBLCL, using the classification of tumours of haematopoietic and lymphoid system [21].

#### Liquid biopsies

Three sets of samples will be collected: the first sample is taken before initiation of chemotherapy, the second sample after the second cycle of chemotherapy, and then at the end of therapy. Nine milliliters of peripheral blood will be collected into BCT®Streck tubes or Roche tubes for cfDNA analysis. Another 4 ml of blood will be collected in EDTA for isolation of PBMCs and frozen at − 70 °C / -80 °C. Both blood draws will occur at the same time as routine blood sampling. Plasma from the cell-free DNA collection tube is then double spun, aliquoted, and frozen at − 70 °C / -80 °C. Frozen plasma samples are batched and shipped from field laboratories under temperature-controlled conditions (dry ice) to a central sequencing laboratory in MUHAS in Tanzania or CPHL in Uganda for analysis.

#### DNA extraction

At the sequencing facility, cfDNA is extracted using QIAamp Circulating Nucleic Acid Kit (Qiagen, USA), as per the manufacturer’s instructions. The yield and size distribution of free-circulating DNA is measured using Qubit 3.0 Fluorometer dsDNA High Sensitivity kit (Thermo Fisher Scientific Inc. USA) and Agilent 2100 Bioanalyzer High Sensitivity DNA assays (Agilent Technologies Inc. USA) respectively.

#### Library preparation and target enrichment

The DNA libraries are prepared using the Thru PLEX Tag-Seq HV kit (Takara Bio Inc. Japan) as per the manufacturer’s instructions. The hybrid capture is performed using IDT xGen Hybridization and Wash Kit (IDT Inc. USA) protocol. Streptavidin-coated magnetic beads are used to bind and extract biotinylated probe-hybridized target DNA. This protocol includes target enrichment by PCR prior to sequencing using KAPA HiFi HotStart Ready Mix and DNA clean up using Agencourt AMPure XP PCR Purification system (Beckman Coulter, USA). The capture library products are assessed using Qubit 3.0 Fluorometer (Thermo Fisher Scientific, USA) and Agilent Bioanalyzer High Sensitivity DNA assay (Agilent Technologies Inc., USA).

#### Sequencing libraries

The target capture library pool is sequenced on the Illumina MiSeq (Illumina, CA, USA) following the manufacturer’s protocol. Our panel design includes known translocation hotspots in MYC, IGH, and IGK, previously described in BL [22], and mutation hotspots in genes known to be recurrently mutated in HL [23].

#### Bioinformatics analysis

The bioinformatics pipeline is built on the Amazon Web Services (AWS) cloud computing system. Paired-end fastq data sequenced using the Illumina MiSeq are cleaned, trimmed, clustered, and deduplicated using bespoke scripts and aligned to the human genome (hg19) using BWA-mem 2 [24]. Variants are annotated using Vardict [25], Varscan 2 [26], and Mutect 2 [27]. Filtering options for SNVs and small insertions and deletions are provided including variant allele frequency (VAF), quality, coverage, and strand bias. Translocations are called using GRIDS S [28], Aperture [29], and SViCT [30] and combined using bespoke scripts. The percentage of ctDNA is estimated using the VAF of known somatic mutations. Variants of known clinical significance including translocations will be combined into a clinical report that can be fed back to clinical scientists as well as be used for research purposes.

#### Follow-up study visits

Patients with a confirmed diagnosis of lymphoma will be followed up 3-monthly for 6 months following completion of their final cycle of chemotherapy. Information reviewed as part of patient follow-up will include medical history – current symptoms, duration of symptoms, the severity of symptoms (graded as per CTCAE v4.03), general physical assessment including assessment of the patients’ peripheries, cardiovascular system, respiratory system, abdominal examination (with documentation of findings including the presence or absence of lymphadenopathy or organomegaly) and ear-nose-throat assessment. Concomitant medications – a list of medication (including any vaccinations) taken by the patient in the 12-weeks before the presentation- will also be asked. SOC blood tests including full blood picture, urea, and electrolytes, liver function, and lactate dehydrogenase will be requested.

#### Data management

For clinical data, we will use a password-protected instance of REDCap stored on a secure server at MNH. Only essential research staff have access to the database. For targeted sequencing data, we will use a HIPAA-compliant cloud. Access will be password protected and restricted to study staff. Patients will be given a unique study ID. In line with ethical procedures, all samples will be anonymised and receive a unique sample ID before transfer to the research laboratory. This sample ID will also be used for the transfer of the data. Reports from standard-of-care tests will be linked to the study IDs by treating clinical teams who will erase patient IDs before reports are given to the research team. All identifiable information will remain at the clinical study sites. Data storage will be on an encrypted and password-secured database in the HIPAA compliant cloud.

#### Statistical analysis and sample size estimation

Sensitivity and specificity will be calculated based on a confusion matrix constructed by applying the test (liquid biopsy) and the gold standard (invasive biopsy and best local histopathology) on several cases (positive for lymphoma) and controls (negative for lymphoma) and comparing their output. We require that, for a reliable test, both metrics are at least 95%. Under this assumption, both sensitivity and specificity can be estimated within a 5% margin of error at a 95% confidence level, given a sample of 73 cases and 73 controls. By relaxing the above reliability requirement to, for example, 80% sensitivity and specificity, the same level of precision would require 246 cases and 246 controls. With 73 cases and 73 controls, on the other hand, the attainable margin of error, in this case, is slightly lower than 10%.

The performance of the test in relation to the gold standard will be assessed by testing whether the observed sensitivity or specificity is significantly lower than the expected value of 95% using the (exact) binomial test. Given 73 cases and 73 controls, we can detect an observed sensitivity or specificity at least 10% lower than the expected value of 95% with 84% power at a 95% confidence level. Detecting smaller differences between observed and expected values requires larger samples. For example, detecting a difference of only 5% with 80% power and 95% confidence would require 203 cases and the same number of controls.

Finally, assuming 73 cases and 73 controls and given the current prevalence of EBVL at 50%, we estimate that 300 patients will have to be screened to generate the number of cases and controls required for our analysis.

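### The accuracy test can show a shortfall from 95% but cannot show adequacy, and the stated 84% power and n = 203 do not match the exact test that is named

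*Protocol article*

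**What the plan says.** All of this is in the protocol article, Methods, under Statistical analysis and sample size estimation.

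- Requirement: "We require that, for a reliable test, both metrics are at least 95"%.
- Precision: at that level, "both sensitivity and specificity can be estimated within a 5% margin of error at a 95% confidence level, given a sample of 73 cases"; the controls number the same.
- Test: performance against histopathology is assessed by "testing whether the observed sensitivity or specificity is significantly lower than the expected value of 95% using the (exact) binomial test".
- Power: with 73 per group, "we can detect an observed sensitivity or specificity at least 10% lower than the expected value of 95% with 84% power"; the confidence level is again given as 95%.
- Larger sample: "detecting a difference of only 5% with 80% power and 95% confidence would require 203 cases and the same number of controls".

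The article gives no test against a minimum acceptable value, and sets no lower confidence limit as a criterion for success. It does not say whether the 95% confidence level means 5% in one tail or 2.5%.

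**The concern.** The requirement and the test point in opposite directions. The requirement asks whether the assay is good enough. The test takes 95% as the null value and looks only for evidence that the truth is lower, so its only favourable outcome is failure to reject. Failure to reject also becomes more likely as the number of evaluable patients falls.

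Two things are at stake. First, the Discussion part of the abstract hopes for proof of principle that ctDNA can serve where pathology is lacking. Such a claim needs positive evidence of accuracy, which this test cannot give. Second, the power and sample size figures are offered as properties of the exact binomial test, and a reader who recomputes that test obtains different numbers.

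**Working it through.** **Inputs, all from Statistical analysis and sample size estimation.** n = 73 per group, reference value 0.95, alternatives 0.85 and 0.90, exact binomial test, lower direction. Alpha is read as one-sided 5%, with 2.5% shown as the alternative. X is the number correctly classified, X ~ Bin(n, p).

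**1. The precision figures reproduce.** n = 1.96² p(1−p)/0.05².
- p = 0.95: 3.8416 × 0.0475/0.0025 = 73.0, as stated.
- p = 0.80: 3.8416 × 0.16/0.0025 = 245.9, so 246, as stated.
- Margin at p = 0.80, n = 73: 1.96 × √(0.16/73) = 9.2%, consistent with slightly under 10%.

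**2. The test as written at n = 73.** Reject at the largest c with P(X ≤ c | 0.95) ≤ alpha.
- One-sided 5%: P(X ≤ 65) = 0.029 and P(X ≤ 66) = 0.072, so reject at 65/73 or fewer. A result of 66/73 = 90.4% (exact 95% CI 81.2% to 96.1%) is not significant.
- One-sided 2.5%: reject at 64/73 or fewer (actual size 0.0105).

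**3. What goes unrejected at one-sided 5%.** P(X ≥ 66 | p):

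| True value | Not rejected |
|---|---|
| 0.90 | 1 − 0.448 = 55% |
| 0.88 | 34% |
| 0.85 | 1 − 0.874 = 12.6% |

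If both metrics are truly 90%, neither is rejected with probability 0.55² ≈ 30%, treating the groups as independent.

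**4. Stated power and n against the named test.** Exact power is saw-toothed in n, so two sample sizes are given: the first n that reaches 80%, and the smallest n from which power stays at or above 80%.

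| Version | Power at 0.85, n = 73 | n for 0.95 v 0.90, first / sustained |
|---|---|---|
| Stated | 84% | 203 |
| Exact, one-sided 5% | 87.4% | 169 / 191 |
| Exact, one-sided 2.5% | 78.5% | 213 / 234 |
| Exact, two-sided 5% (minimum likelihood) | 87.4% | 191 / 213 |

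No exact version in the written direction gives 84%, and in none is 203 the first or the sustained n.

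**5. The reverse test, one-sided 5%.**
- H0 p ≤ 0.85, truth 0.95, n = 73: P(X ≥ 68 | 0.85) = 0.0286, so success needs 68/73 (93.2%). Power is P(X ≥ 68 | 0.95) = 84.2%.
- H0 p ≤ 0.90, truth 0.95: power first reaches 80% at n = 179 and stays there from n = 203. At 203, success needs 190, the actual size is 0.0495 and power is 85.9%.

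Both stated figures coincide with this test, 203 under the sustained-power convention.

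**6. What 73 per group can show.**
- Excluding 85% at a true 95%: 84.2% power per metric, and 0.842² = 0.709, about 71%, for both.
- Excluding 95% itself: 0.95⁷³ = 0.024, whereas allowing one error gives 0.024 + 73 × 0.05 × 0.95⁷² = 0.115, above 5%. All 73 must therefore be correct. Power is 0.97⁷³ = 11% at a true 97% and 0.99⁷³ = 48% at a true 99%.

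**The case against.** The strongest reply has four parts.

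*The protocol never says that a non-significant result means the assay is reliable.* True. The 95% requirement stands as a separate sentence, 73 per group is justified first by precision, and those figures reproduce. A reader might infer that 66/73 would be declared a pass. The documents do not say so, and 90.4% would still lie below the stated requirement. What remains is that the only inferential test described cannot deliver a positive conclusion, and no other criterion shows how the requirement would be judged met.

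*The origin of 84% and 203 is unknown.* Also true. A reader might infer that they were computed for the reverse test. The match is close, but 203 depends on the sustained-power convention, and a two-sided continuity-corrected normal approximation in the written direction comes near (84.9%, n = 205). That approximation is not the exact test named, so the mismatch stands whatever its source.

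*The discrepancy is harmless.* At one-sided 5% it is conservative: the named test has more power than stated and needs fewer patients. At one-sided 2.5% the stated 84% is too high (78.5%) and 203 is too few. The article does not say which applies.

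*Accuracy does not decide anything.* It is a secondary endpoint, the primary being time to diagnosis, and under Study monitoring and safety discordant cases are managed on routine pathology. A reader might treat the test as the gate for adoption, but no adoption decision is tied to it. This lowers the severity. It does not remove the point, because the accuracy calculations are the only stated basis for 146 patients. The article also says openly that smaller differences need larger samples, which is fair disclosure of the weakness at 90%.

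**Conclusion.** The point holds in this form: a test for a shortfall from 95% cannot show that a requirement of at least 95% is met, and the stated planning figures do not reproduce under the exact test that the article names. At n = 73 and one-sided 5%, the test leaves a true 90% unrejected 55% of the time, though a true 85% only 12.6%. Stated power differs from exact power by 3.4 points at one-sided 5% (84% v 87.4%) and by 5.5 points the other way at 2.5% (84% v 78.5%).

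This assumes that all 73 per group are evaluable, that the confidence level corresponds to one of the alphas shown, and, for joint figures, that the two groups are independent. It does not support saying that the sponsor will treat non-significance as success, that the figures certainly came from the reverse test, or that the sample is too small for the test as written at one-sided 5%. Severity: should fix, since accuracy is secondary but drives the sample size.

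**What to change.** Change the wording of Statistical analysis and sample size estimation, or carry the change in the SAP:

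1. State that a result not significantly below 95% is not evidence of reliability.
2. Have the investigators pre-specify a minimum acceptable sensitivity and specificity, with reasons, and require the one-sided exact lower confidence limit of both metrics to exceed it. The article gives no such minimum, and it should not be chosen because it reproduces 84%.
3. State alpha and sidedness. This matters at the margin: 68/73 against a minimum of 85% has p = 0.0286, which passes at one-sided 5% and fails at 2.5%.
4. Restate power for that test, per metric and jointly, and replace or re-derive 84% and 203, naming the method and the convention for saw-toothed power.

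For information when choosing the minimum: 73 per group gives 84% power per metric, about 71% jointly, to exclude 85% at a true 95% with one-sided 5%. It cannot realistically demonstrate at least 95%, so that requirement should be described as a target for the estimate or supported by a larger sample.

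Cost: wording only, with no extra patients unless a stricter minimum is chosen. The downside is that the joint power to be reported is less favourable than the 84% now stated.
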